#### Outcome Measures

The primary outcome measure is the time spent on health information management per consultation. We defined health information management as the preparations and executions of collection, aggregation, analysis, and dissemination of clinical data, both at the individual and aggregate levels [26]. To tailor the general definition of the primary outcome to fit our context, we first used workflow mapping exercises ahead of data collections for the eRegTime study (as described previously) to list all the tasks usually done by the nurse or midwife in the primary health care clinics during antenatal care on a typical workday [27]. We then defined 6 activity types corresponding to the tasks: accessing information, reporting, documentation, client care, client-related care, and miscellaneous. The primary outcome measure—health information management time—was defined as time spent on all tasks involving the activity types “information access,” “information documentation,” and “information reporting” (see Table 1) [27]. “Information access” includes all activities that involve seeking and finding relevant existing health or demographic information on the client [27]. “Information documentation” consists of all tasks that involve writing down client information in the antenatal records (electronic or paper), laboratory, and ultrasound forms [27]. “Information reporting” is defined as transferring information from the antenatal records and registers for public health reporting [27].

A total of 2 additional analysis categories were defined: (1) “client care” that includes all activities in which the care provider is fully focused on the client without any writing and (2) “client-related care” that refers to all tasks that are imperative for care of individual pregnant women undertaken between 2 antenatal care consultations (see Table 1).

Activities unrelated to care of clients, including personal activities of the care providers, and tidying and preparing the consultation room for new clients, were categorized as “miscellaneous” (see Table 1) [27].

**Table 1 table1:** Analysis categories including the primary outcome measure, corresponding task, and task category as defined for data collection (adapted from the study by Pizziferri et al [30] and tailored to the local context).

Analysis category	Task category in data collection tool	Name of task in data collection tool
Client care	Outside	Assisting doctor

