Client care	Outside	Examination in other room
Client care	Procedures	Clinical and medical examination
Client care	Procedures	Injections and bloodtake
Client care	Procedures	Giving tablets
Client care	Procedures	Other
Client care	Talking	Education and counseling
Client care	Talking	Talking to family
Client care	Talking	History: demographic and medical
Client care or client-related care^a^	Talking	Clinical support
Client care or client-related care^a^	Talking	Call client or family
Client care or client-related care^a^	Talking	Referrals
Client care or client-related care^a^	Talking	Other
Health information management	Between or after consultations	Writing in statistics book
Health information management	Computer-Find	Client file
Health information management	Computer-Find	Lab or ultrasound results
Health information management	Computer-Writing	Client file (including history)
Health information management	Computer-Writing	Lab or ultrasound form
Health information management	Computer-Writing	Schedule appointment
Health information management	Computer-Writing	Text message in eRegistry
Health information management	Paper-Find	Client file
Health information management	Paper-Find	Lab or ultrasound results
Health information management	Paper-Writing	MCH (Maternal and Child Health) Handbook (including history)
Health information management	Paper-Writing	Client file (including history)
Health information management	Paper-Writing	Register book
Health information management	Paper-Writing	MCH Handbook or register book
Health information management	Paper-Writing	Register book or client file
Health information management	Paper-Writing	Client file or MCH handbook
Health information management	Paper-Writing	Lab, ultrasound, prescriptions, and referrals
Health information management	Paper-Writing	Schedule appointment
Health information management	Paper-Writing	Writing on other paper
Health information management	Talking	Explaining test results
Health information management	Talking	Technical support
Health information management or client-related care^b^	Computer-Read	Appointment list
Health information management or client-related care^b^	Computer-Read	Client file
Health information management or client-related care^b^	Computer-Read	Lab or ultrasound results
Health information management or client-related care^b^	Computer-Read	Guidelines, treatment
Health information management or client-related care^b^	Computer-Read	Other info

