Health information management or client-related care^b^	Paper-Read	Appointment list
Health information management or client-related care^b^	Paper-Read	MCH handbook
Health information management or client-related care^b^	Paper-Read	Client file
Health information management or client-related care^b^	Paper-Read	Lab or ultrasound results
Health information management or client-related care^b^	Paper-Read	Treatment guidelines
Health information management or client-related care^b^	Paper-Read	Other info
Miscellaneous	Between or after consultations	Cleaning, arranging files
Miscellaneous	Between or after consultations	Phone and computer (personal)
Miscellaneous	Between or after consultations	Other: praying, eating, toilet
Miscellaneous	Between or after consultations	Eating, praying, toilet
Miscellaneous	Between or after consultations	Group education
Miscellaneous	Postpartum care	Postpartum care

^a^Task classified as client-related care if done outside of a consultation. If done within an antenatal care consultation, it is classified as client care.

^b^Task classified as client-related care if done outside of a consultation. If done within an antenatal care consultation, it is classified as health information management.

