#### Sampling

For sample size estimations, we assumed that clinics using paper-based systems spend an average of 10 min on health information management per client. We also assumed unequal and higher SD around the mean health information management time (in minutes) for clinics that use the eRegistry (SD=5) compared with clinics that use paper-based systems (SD=2) because of an expected variance in computer literacy and confidence of use. Sample size calculations were made using the Stata command “clustersampsi” to detect a 25% difference at a 90% power and 5% significance using an a priori intracluster correlation coefficient of .1 [28,29]. A total of 24 primary health care clinics were selected to be observed, 12 from each arm of the CRCT, with at least 8 observed antenatal consultations per clinic (Figure 1). Statisticians that are independent of the eRegTime study team performed a random sampling of the primary health care clinics for the observations, stratified on laboratory availability.

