#### Data Collection Methods

We designed the data collection tool based on a Microsoft Access database template made available online by the US Agency for Healthcare Research and Quality [24], customized to the clinical workflow in the West Bank. The data collection tool was installed on handheld tablets. The data collection tool contains a list of tasks categorized under 10 task categories, and every task can be time-stamped (Figure 2) [30,31]. The task categories covered the care providers’ entire workday consisting of every clinical and nonclinical task, including after-consultation and between-consultation work.

The observers were trained to first determine the nature of the observed task and then click on the corresponding task on the data collection tool (Figure 2) [32]. The observer could end a task by clicking on the “confirm entry” button (Figure 2). In case of multitasking by the care providers, the observers were instructed to select the principal activity. After-consultation work were recorded as separate observations, as were postpartum care consultations.

The database stored the observation times for each task with an activity code linked to the tasks. In accordance with ethical approvals for the study, no personal or other demographic data related to the client or the care provider were collected, and clinic names were only being stored as computer-generated codes in the database.

A total of 4 trained observers completed the data collection. Observers were trained with simulation videos on the time-motion methodology and the task categories and in using the data collection tool (see Multimedia Appendix 3). Following training, the observers conducted practice observations in nonstudy clinics with and without the eRegistry. After this, observations and data collections were undertaken in the study clinics. The observers recorded a full workday and included all the antenatal consultations during that day. If the required number of antenatal consultations per clinic (n=8) was not achieved in 1 day, additional days of observation were carried out until the required cluster size was reached.

The field coordinators of the study received the data after each day of data collection and checked that the sample size for each clinic is reached with a sufficient number of documented observations.

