### Data Analyses

The unit of measurement of the primary outcome is the time spent on health information management per client per care provider, where time will be analyzed in minutes. Statistical analyses will be performed using Stata version 15 or later (StataCorp LLC, 2017,  *Stata Statistical Software: Release 15*) or RStudio version 1.2.1335 or later. Descriptive statistics for the time variables will be summarized as means and SDs. We will report on the average time spent on antenatal consultation overall, and for booking visits and other antenatal visits separately, and the average time spent on each of the activity types including those that are not part of the primary outcome (including “client care,” “client-related care,” and “miscellaneous”; see Table 1).

We assume that the nurse or midwife spends, on average, an equal amount of time on after-consultation documentation work per client. The after-consultation time spent on client-related documentation and public health reporting will be averaged over the number of observed antenatal consultations and added to the time spent per consultation. Differences in the health information management time between the clinics with and without the eRegistry will be tested for significance using the linear mixed effects model to account for clustering [33,34]. In addition, as secondary analyses, we will test for differences in the health information management time separately for booking visits and other antenatal visits, and differences in time spent on other activity types in the 2 arms. Postpartum care consultations will be excluded from the analysis, as the focus of both eRegQual and eRegTime studies is on antenatal care quality and clinical processes.

Accompanying the results of the outcomes of the study, interobserver reliability assessments will be reported using kappa coefficients for the total number of clinical tasks and activity types recorded and intraclass correlation coefficients for the recorded mean times for the tasks and analysis categories (see Table 1) [35].

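### The rule for adding outside-consultation time is narrower than the primary outcome: finding records outside consultations, and on a literal reading finding or writing between them, has no stated route in

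*Protocol article*

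**What the plan says.** The protocol article deals with this outcome in three places.

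- **Definition (Outcome Measures).** Health information management time "was defined as time spent on all tasks involving the activity types" access, documentation and reporting. Access is a type of its own: it "includes all activities that involve seeking and finding relevant existing health or demographic information on the client". The definition does not restrict any of the three to time inside a consultation.
- **Classification (Table 1).** The Computer-Find, Paper-Find, Computer-Writing and Paper-Writing rows are health information management with no footnote. So is "Writing in statistics book", which sits in the task category for work between or after consultations. Only the Read rows depend on timing within this category. Footnote b makes them client-related care outside a consultation, and says of them: "If done within an antenatal care consultation, it is classified as health information management".
- **Recording and derivation.** Under Data Collection Methods, the task list covers the whole workday, "including after-consultation and between-consultation work". That section adds: "After-consultation work were recorded as separate observations, as were postpartum care consultations". Under Data Analyses, the outcome is the time per consultation plus one averaged component: "The after-consultation time spent on client-related documentation and public health reporting will be averaged over the number of observed antenatal consultations".

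**The concern.** The derivation does not produce the variable that the definition describes. A minute spent finding a client file or a laboratory result after the last consultation is health information management under Table 1. It is neither documentation nor reporting, so the add-back sentence does not pick it up. Find or writing time between two consultations has a similar problem if after-consultation is taken at its word, because Data Collection Methods names between-consultation work separately.

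This bears on the comparison itself. The section on workflow in eRegistry clinics says that clinical tasks are the same in both arms and that only health information management differs. Any such time left out is therefore of the kind being compared, and the amount left out could differ by arm. Two analysts working from the same time stamps could also compute different primary outcomes, each with support in the text.

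**Working it through.** **1. Trace each kind of outside-consultation time through the texts.**

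| Time outside a consultation | Table 1 class | Reached by the add-back sentence? |
|---|---|---|
| Writing after consultations (records, registers) | Health information management, no footnote | Yes, as documentation or reporting |
| Statistics book after consultations | Health information management, no footnote | Yes, as reporting |
| Find (file, laboratory or ultrasound results) after consultations | Health information management, no footnote | No: access is not named |
| Find between consultations | Health information management, no footnote | No: neither access nor between-consultation time is named |
| Writing between consultations | Health information management, no footnote | Not on a literal reading; yes if after-consultation covers all outside time |
| Read tasks, between or after | Client-related care (footnote b) | Not applicable: excluded by design |

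The Find rows are the firmest case, because they fall outside the sentence however after-consultation is read. The writing row depends on that reading.

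**2. A competing definition.** Outcome Measures also describes client-related care as tasks needed for individual women that are undertaken between two antenatal consultations. Taken alone, that could claim between-consultation Find and writing time. Table 1 gives those rows no such condition, so the two passages need reconciling as well.

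**3. The study's own target.** Inputs from Sampling: "clinics using paper-based systems spend an average of 10 min on health information management per client"; a 25% difference; SD 2 min (paper) and 5 min (eRegistry); intracluster correlation 0.1; 8 consultations per clinic; 12 clinics per arm; 90% power; 5% significance, taken here as two-sided.

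- Target difference: 0.25 × 10 = 2.5 min.
- Consultations per arm without clustering: (1.960 + 1.282)² × (2² + 5²) / 2.5² = 48.75, rounded up to 49.
- Design effect: 1 + (8 − 1) × 0.1 = 1.7.
- Clinics per arm: 49 × 1.7 / 8 = 10.4, so 11 by the normal approximation.
- Power from the noncentral t on 2k − 2 degrees of freedom: 88.8% with 11 clinics per arm and 91.5% with 12. Twelve is the smallest number reaching 90%, so the stated figure reproduces. The normal approximation at 12 gives 93.7%.

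**4. Illustration only.** The documents give no amount for Find or writing time outside consultations. Suppose the omitted time differs between arms by g min per client, in the direction that shrinks the difference, with the SDs unchanged. The standard error at 12 clinics per arm is √(29 × 1.7 / 96) = 0.717 min. Power is approximately Φ((2.5 − g)/0.717 − 1.960).

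| Assumed gap g (min per client) | Share of 2.5 min | Apparent difference (min) | Approximate power |
|---|---|---|---|
| 0 | 0% | 2.5 | 93.7% |
| 0.25 | 10% | 2.25 | 88% |
| 0.5 | 20% | 2.0 | 80% |
| 1 | 40% | 1.5 | 55% |
| 2 | 80% | 0.5 | 10% |

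A gap of the opposite sign would enlarge the apparent difference instead. At 8 consultations per clinic, 1 min per client is 8 min of a clinic's observed time.

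**The case against.** The strongest reply is that nothing in the article says this time is dropped. Outcome Measures governs what is counted, and the add-back sentence may only explain how pooled time is shared out per client. Table 1 uses one joint category for work between or after consultations, so after-consultation may be shorthand for all outside time. Completing a woman's record once she has left can fairly be called after-consultation documentation. The article also does not say when a consultation observation starts, so pulling the next woman's file may be logged within her visit.

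Much of this stands for writing, which is why that part is put only as a literal reading. It does not rescue Find time outside consultations: the shorthand widens when the work is done, but the sentence still names only documentation and reporting. Nor is this detail left to an analysis plan. The derivation is stated, and it conflicts with the stated definition.

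A reader might infer that all information work between consultations is lost. The documents do not support that, because footnote b deliberately assigns reading outside consultations to client-related care. A reader might also infer that the rule understates the burden in paper clinics, on the idea that paper files are pulled outside visits. The workflow section for paper clinics does not describe this. The eRegistry workflow points to a possible loss in the other arm, since laboratory results arriving on paper are entered retrospectively and may have to be found first.

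**Conclusion.** The point holds as a mismatch between a stated derivation and a stated primary outcome. Find time outside consultations has no stated route into the per-client outcome. Find or writing time between consultations has none on a literal reading. Table 1 classes both as health information management whenever they are done.

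The effect on the arm comparison cannot be derived from the documents, in size or in sign. The power figures above rest on assumed gaps and show only that a fraction of a minute per client would matter against a 2.5 min target. The sample size itself is not in question. The rule should be settled before results by arm are seen, because it determines how the primary outcome is built.

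**What to change.** Replace the add-back sentence in Data Analyses with:

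> All time on tasks that Table 1 classes as health information management when done outside a consultation, whether between or after consultations and excluding time recorded as postpartum care, is averaged over the observed antenatal consultations and added to the health information management time within each consultation.

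Pointing to Table 1 is safer than listing tasks. It keeps the Read rows out, as footnote b intends. It also brings in two Talking rows that carry no footnote and that a list of Find and Writing tasks would miss: explaining test results and technical support.

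In Outcome Measures, reconcile the description of client-related care as work between two consultations with Table 1, so that Find and writing tasks done at that time belong to one category only.

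The cost is one sentence, one clarification and a change to the derivation code. No new data are needed. There is a small downside: some outside-consultation time that cannot be tied to antenatal clients may be included, since the same staff also care for postpartum women and newborns. The current averaging rule already carries that risk.

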### Workflow in Primary Health Care Clinics

#### Workflow in Clinics Using Paper-Based Systems

Pregnant women visit primary health care clinics for their first antenatal (booking) visit on specific workdays (clinics may work 1-4 days a week). The nurse or midwife in the clinics receives the pregnant women for the booking visit and documents a set of demographic data (eg, name, national identification number, address, phone number, and date of birth), and medical, surgical, and obstetric history. Afterward, the nurse or midwife measures and documents the woman’s height and weight, blood pressure, and fundal height and orders and fills out routine laboratory results appropriate for each antenatal visit. As part of the booking visit, the doctor examines women on the same workday or a few workdays later in some clinics. The nurse or midwife assists the doctor in medical and ultrasound examinations. For pregnant women identified with risk factors that warrant a referral, the nurse or midwife makes necessary arrangements for transfer to the referral health facility. There is a flexible appointment system for all subsequent antenatal visits. For uncomplicated pregnancies, the nurse or midwife documents blood pressure and fundal height, checks for fetal presentation, and orders laboratory investigations during the subsequent antenatal visits. Nurses and midwives typically do client care for pregnant and postpartum women as well as newborns in the first part of the workday. Following this, the nurse or midwife usually completes registers for antenatal care, referrals, ultrasounds, vaccines, and laboratory investigations. The nurse or midwife also compiles the data in the registers for public health reporting to the Palestinian Ministry of Health, typically concentrating this task in 1 or 2 workdays monthly. Event counts of number of pregnancies registered in the clinic, number of ultrasound examinations and laboratory tests that are performed, and number of pregnancies with risk conditions that are referred are some examples of the data that are part of standardized monthly reports submitted by care providers [25].

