### Ethics Approval and Consent to Participate

The eRegTime study was approved by the Palestinian Health Research Council (PHRC/HC/208/17) and the Regional Committee for Medical and Health Research Ethics in Norway (2017/400). Permissions to conduct observations in the clinics have been obtained from the Palestinian Ministry of Health. Care providers and supervisors of the primary health care clinics will be informed of the data collection for this study. Considering the local sensitivity and hesitance related to signing documents in our study context, pregnant women will be asked for oral consent to allow the observers to be present in the rooms during consultations, and the ethics committees were notified of this. No data will be recorded on personal or individual characteristics of pregnant women, care providers, or primary health care clinics. Only completely anonymous data will be available to the researchers for analysis.

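### The after-consultation part of the primary outcome divides work that is not restricted to antenatal clients by antenatal consultations alone

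*Protocol article*

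**What the plan says.** The primary outcome is health information management time per antenatal consultation. Data Analyses fixes how work done outside consultations enters it: "The after-consultation time spent on client-related documentation and public health reporting will be averaged over the number of observed antenatal consultations", and the quotient is added to each consultation's own time. The stated premise is "We assume that the nurse or midwife spends, on average, an equal amount of time on after-consultation documentation work per client". The same section adds "Postpartum care consultations will be excluded from the analysis".

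The section on workflow in paper clinics describes the working day behind those minutes: "Nurses and midwives typically do client care for pregnant and postpartum women as well as newborns in the first part of the workday". Afterwards the nurse or midwife "usually completes registers for antenatal care, referrals, ultrasounds, vaccines, and laboratory investigations". Monthly reporting is a separate burden, "typically concentrating this task in 1 or 2 workdays monthly".

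Data Collection Methods records after-consultation work and postpartum consultations as separate observations. In Table 1 the codes for register-book and statistics-book writing count as health information management and carry no client type. Postpartum care has a single code, classed as miscellaneous. In eRegistry clinics, clinical data are entered during the consultation and monthly reports are automatic, but laboratory results are still typed in later.

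**The concern.** The denominator counts antenatal consultations. The numerator, as far as the article defines it, is whatever register and reporting work the observer logged after consultations. Excluding postpartum consultations removes the visits. It does not remove register entries made later for those clients. The premise of equal time per client also fits poorly with a denominator that leaves out some of the clients.

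This concerns the sole primary outcome, and the mismatch need not cancel between arms. On paper, a postpartum client's register entry tends to come after client care, so it can be charged to antenatal clients. With the eRegistry, which also covers postpartum and newborn care, the corresponding entry tends to fall inside the postpartum observation and so outside the outcome. Part of an apparent time saving could then come from the apportioning rule.

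**Working it through.** **The plan's own figure.** The Sampling section gives SDs of 2 (paper) and 5 (eRegistry), a 25% change from 10 min (2.5 min), 90% power, 5% significance (taken as two-sided), ICC 0.1, and 8 consultations in each of 12 clinics per arm.

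- Without clustering: n = (1.960 + 1.282)² × (2² + 5²) / 2.5² = 48.8 per arm.
- Design effect: 1 + (8 − 1) × 0.1 = 1.7, so 82.9 consultations per arm, or 10.4 clinics. With t quantiles on 22 df this becomes 11.4, which rounds up to the planned 12.
- Design standard error of the arm difference: √(29 × 1.7 / 96) = 0.717 min.

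The sample size is reproduced, and this point does not affect it.

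**What the rule returns.** Let a be true after-consultation minutes per antenatal client, r the number of non-antenatal clients per antenatal client, and f the after-consultation work of a non-antenatal client relative to an antenatal one. If other clients' work is in the numerator:

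- antenatal-only denominator (the plan): a(1 + r f), an excess of a r f;
- all-client denominator: a(1 + r f)/(1 + r), a shortfall of a r(1 − f)/(1 + r).

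For any f from 0 to 1 the two values bracket a. With D = a_paper − a_eReg, and r and f the same in both arms, the apparent saving (paper minus eRegistry) is biased by D r f under the plan's rule and by −D r(1 − f)/(1 + r) under the alternative.

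**Illustration.** The article gives none of a, r or f. Assume D = 2.5 min (for example 3 min on paper and 0.5 min with the eRegistry) and r = 0.5:

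| f | Bias, antenatal-only (min) | Bias, all clients (min) |
|---|---|---|
| 0 | 0 | −0.83 |
| 0.2 | +0.25 | −0.67 |
| 0.4 | +0.50 | −0.50 |
| 1 | +1.25 | 0 |

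Under the plan's rule, 0.25 min is 10% of the 2.5-min target and 0.25/0.717 = 0.35 standard errors. A bias of 1.25 min is 50% of the target and 1.74 standard errors. The two rules are equally wrong at f = 1/(2 + r), which is 0.4 here.

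**Range at f = 1, for r from 0.1 to 1.** D = 1 gives 0.10 to 1.00 min, D = 2 gives 0.20 to 2.00 min, D = 0 gives none, and D = −1 gives −0.10 to −1.00 min, against the eRegistry.

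**If f differs by arm.** Suppose postpartum eRegistry entry falls wholly inside postpartum observations (f = 0), while paper has f = 1. With 3 and 0.5 min and r = 0.5, the true difference is 2.5 min.

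- Antenatal-only: 3 × 1.5 − 0.5 = 4.0 min.
- All clients: 3 × 1.5/1.5 − 0.5/1.5 = 2.67 min.
- Paper lower bound minus eRegistry upper bound: 3.0 − 0.5 = 2.5 min.

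Both same-denominator contrasts overstate the saving in this case. The cross-comparison does not.

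**The case against.** The strongest reply is that the numerator may already be antenatal. Outcome Measures ties documentation to antenatal records and to laboratory and ultrasound forms, and postpartum care has its own code outside the outcome. Observers may have logged postpartum paperwork under that code. The training manual could settle this but is not shown. That stands: a numerator covering all clients is an inference from the workflow, Table 1 and Data Collection Methods, and is not stated.

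It is also fair that other clients may create little register work. The listed registers include none named for postpartum or newborn care, and the list does not say whose vaccine or laboratory entries are meant. A small f makes the bias small, and below f = 1/(2 + r) an all-client denominator would be further from the truth than the plan's. That rules out simply swapping denominators.

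Three stronger readings are tempting and are not supported.

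- *Only the paper arm is inflated, creating a saving where none exists.* The same rule applies to both arms, and retrospective laboratory entry leaves after-consultation work in the eRegistry arm. With equal r and f, a biased contrast also needs a real after-consultation difference, so a true overall null would require that difference to be cancelled exactly within consultations.
- *The false-positive rate is known to be high.* At the design standard error with 22 df, a bias of 0.25 min would reject a true null about 6% of the time and 1.25 min about 38%. Those rates come entirely from assumed minutes, client mix and workload.
- *Women who decline observation add to the error.* The article says only that "pregnant women will be asked for oral consent to allow the observers to be present in the rooms during consultations". It reports no refusals, and Data Collection Methods says every antenatal consultation of the day was included.

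Concentrated monthly reporting could make sampled days miss paper-arm work, which pulls the other way. That is a separate sampling question and does not repair the mismatch.

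**Conclusion.** The concern holds as a mismatch between numerator and denominator in the primary outcome. Followed as written, the rule can charge other clients' register work to antenatal consultations, and it fits badly with the plan's own per-client premise. The likely direction favours the eRegistry, because paper registers are filled after client care while eRegistry entry is mostly made during the consultation. Neither direction nor size can be established from the article. Under the stated assumptions (D = 2.5 min, r = 0.5, both equal across arms where relevant) the bias runs from 0.25 min at f = 0.2 to 1.25 min at f = 1. It vanishes if the numerator was in fact limited to antenatal work, if f = 0, or if D = 0 with equal r and f. That range is wide enough to matter against a 2.5-min target, so the rule should be settled before the arms are compared.

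**What to change.** State that the numerator contains only after-consultation time identifiable as antenatal, and say how the codes identify it. Where they do not, compute the outcome twice: once divided by antenatal consultations, and once by all logged antenatal plus postpartum consultations on the observed days. Present the two as upper and lower bounds on per-client time in each arm, and claim a time saving only if it holds under both. Because the relative workload may differ by arm, also report the paper lower bound against the eRegistry upper bound.

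The cost is small. Postpartum consultations are already logged as separate observations, so no new data are needed and the sample size is unchanged. The downsides are some extra analysis, a possibly less favourable estimate, and an incomplete all-client count: Table 1 has no newborn code, so newborn-only clients may not be countable. The bounds also assume that a non-antenatal client creates no more after-consultation work than an antenatal one.
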